### Randomization

Of 15 wards (clusters), 1 ward will be excluded by lottery method before randomization. Clusters will be randomly assigned to intervention and control areas using a 1:1 allocation ratio. Randomization will be done before the participants are recruited. Research teams responsible for identifying potential participants, obtaining consent, and recruiting trial participants will be blinded to the participants’ allocation status. The following steps will be taken to avoid selection bias during random allocation: (1) clusters will be randomized only after the baseline survey; (2) clusters will not be withdrawn from or added to the study; and (3) an epidemiologist who does not come in contact with the study will randomize the clusters.

### Inclusion and exclusion criteria

People 25–65 years of age who are listed in the voter list of 2007 are eligible for inclusion in the baseline survey. The primary endpoint of the study is a reduction in SBP, because with aging there is an increase in SBP due to aortic stiffening [24]. This may not be modifiable through reduction in risk factors. Hence, we have defined an adult population within an age range who will likely respond to reductions in hypertension risk factors through educational interventions. Participants for the blood pressure education intervention study will be chosen from among the respondents who participated in the baseline survey and who live in a ward in the study area. Persons who are severely ill, who are unlikely to be in the community throughout the intervention, who are pregnant women, and who decline consent will be excluded from the study.

### Primary and secondary outcomes

The primary outcome of the study is a reduction in mean SBP among normotensive, prehypertensive, and hypertensive populations. The secondary outcomes of the study are reductions in mean diastolic blood pressure and proportion of risk factors (smoking, alcohol, salt intake, body mass index).

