**Methods/design:**

The objective of the present study is to determine the effect of family-based home health education and blood pressure monitoring by trained female community health volunteers. The primary outcome is change in mean systolic blood pressure. A community-based, open-masked, two-armed, cluster-randomized trial will be conducted in Lekhnath Municipality of Nepal. The municipality is divided into 15 administrative clusters. Randomization will be conducted for 14 clusters: 7 for the intervention arm and 7 for the control arm. The participants were recruited from a prevalence study conducted earlier. On the basis of population proportion size, 929 individuals for the intervention group and 709 individuals for the control group will participate in the study. Due to the nature of the study, study participants are not compensated or insured. As part of the blood pressure intervention, trained female community health volunteers will conduct home visits for health education and blood pressure measurement. The primary outcomes will be modeled by using multiple linear regression analysis.

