### Recruitment

A population framework of all eligible participants will be prepared from the voter list prepared by the Election Commission in 2007. As of 15 December 2006, all the people included in the voter list were at least 18 years old. By 2015, all the people in the voter list were at least 25 years of age. The voter list also contains information about the household. Using the voter list, a survey will be carried out by trained health professionals such as nurses and health assistants to estimate the proportion of hypertension in the municipality as well as to prepare a list of eligible respondents to participate in our randomized controlled trial. The data enumerators will receive 5 days of intensive training before collecting data.

If there is more than one participant from the same household eligible to participate in the study at the time of data collection, the Kish method will be adopted to select the participant [22]. The survey tool will be adapted from the World Health Organization (WHO) STEPwise approach to surveillance [23], which includes physical measurement (height, weight), sociodemographic information (e.g., age, sex, family size, occupation, income, education), lifestyle factors (e.g., salt consumption, smoking, alcohol, physical activity), and blood pressure measurement. The classification of normotension, prehypertension, and hypertension is shown in Table 1.

**Table 1 Tab1:** Classification of normotension, prehypertension, and hypertension

SBP/DBP level, mmHg	Taking antihypertensive medication	Status for recruitment
< 120/80		
Yes	No	Normotensive
No	Yes	Hypertensive
≥ 120/80 and < 140/90		
Yes	No	Prehypertensive
No	Yes	Hypertensive
≥ 140/90		
Yes	No	Hypertensive
No	Yes	Hypertensive

*DBP* diastolic blood pressure, *SBP* systolic blood pressure

During that survey, normotensive, prehypertensive, and hypertensive participants will be identified and asked to participate in the study. From among eligible participants, the required sample size of respondents will be chosen in proportion to the population of the specific ward to be sampled. On the fifth day of training, FCHVs from one cluster will sit together and allocate the number of households that has to be visited on the basis of the baseline survey. After that, FCHVs will visit each household, meet the selected participant, and ask for consent to participate in the trial.

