### Intervention

After randomization, the FCHVs participating in the intervention wards will receive a 5-day training package featuring (1) introduction and importance of noncommunicable disease and/or hypertension; (2) identifying populations at risk using a checklist comprising level of salt intake, physical inactivity, smoking, and alcohol consumption; (3) blood pressure screening by using digital sphygmomanometers, height and weight measurement, and referral for those whose blood pressure is > 140/90 mmHg; (4) providing health education in major risk factors; and (5) recording, reporting, and follow-up. Educational sessions are guided by use of the Health Belief Model [28], and training materials will be developed by involving local major stakeholders. The developed materials will be pretested with the FCHVs of Pokhara Municipality.

After receiving the training, the FCHVs will be given a digital sphygmomanometer, manual weighing scale, clinical measuring tape for height, an FCHV manual, and a recording register. During the training program, FCHVs will allocate the households themselves. On average, 1 FCHV will visit 25 households (13 normotensive, 5 prehypertensive, and 7 hypertensive). Each FCHV will visit selected households three times during 1 year, where the FCHV will provide counseling and measure the blood pressure as well as the height and weight of selected respondents. If the participant is hypertensive, the FCHV will ask the respondent to visit the health facility for further diagnosis and treatment. For hypertensive participants, the FCHV will also monitor whether the respondent is taking medicine as per the advice of health care workers. Participants in the control clusters will receive usual care. Usual care means current practices related to hypertension management at the community level. After the 1-year period of the intervention, a follow-up survey will be carried out through trained professional health workers such as nurses and health assistants.

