### Data analysis

The quantitative analysis will be done using STATA version 14 software (StataCorp, College Station, TX, USA) following the Consolidated Standards of Reporting Trials (CONSORT) guidelines for cluster-randomized trials. Flowcharts (Fig. 1) will include the number of participants seen at each stage of the trial, including the number screened, eligible, randomized, and analyzed for the primary outcome. In initial analysis, we will compare baseline characteristics of enrolled participants in the study intervention arm and follow-up status. The primary analyses will be intention to treat at the 12-month follow-up, adjusted for the baseline measure of the outcome. In the event that randomization does not control for differences between the treatment and control groups on baseline characteristics, we will statistically control for those differences in subsequent analyses of program effects. The final outcome will be modeled by using random - effects regression models. The effect size will be reported as mean differences with 95 % CIs for primary data.

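### Body mass index is named as a secondary outcome only as a proportion, although it is measured on a continuous scale; a baseline-adjusted mean would be more sensitive to the modest shifts expected

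*Protocol article*

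**What the plan says.** The section Primary and secondary outcomes gives the secondary outcomes as "reductions in mean diastolic blood pressure and proportion of risk factors (smoking, alcohol, salt intake, body mass index". On the plain reading, the word mean belongs to diastolic pressure and the word proportion to the whole bracketed list, BMI included. No other section makes BMI a mean.

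Under Recruitment, the baseline survey tool is described as one "which includes physical measurement (height, weight"), so BMI can be computed for each person. The same section lists "lifestyle factors (e.g., salt consumption, smoking, alcohol, physical activity") without a unit or response scale for salt. Under Intervention, the volunteers use a "checklist comprising level of salt intake, physical inactivity, smoking, and alcohol consumption", again without a scale. They make three visits in a year and also record height and weight. "After the 1-year period of the intervention, a follow-up survey will be carried out" in the same section.

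Under Data analysis, the primary analyses are intention to treat at 12 months, adjusted for the baseline value of the outcome, with random-effects regression. "The effect size will be reported as mean differences with" confidence intervals, but only for primary data. No effect measure is given for the risk factors.

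**The concern.** BMI is a measured quantity that tends to track closely within a person over a year. Expressed as a share above a cut-off, it registers only the people who cross the line. A participant who loses weight but stays on the same side counts as unchanged. A short education programme would be expected to shift many people slightly rather than move many across a threshold. The Background itself argues from modest shifts in blood pressure across a population.

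The plan keeps systolic and diastolic pressure as means and gives no reason for treating BMI differently. At stake is precision on one named secondary outcome: a real but small fall in BMI is less likely to be seen if only the proportion is compared.

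**Working it through.** The article states no sample size, power, cut-off or prevalence for BMI, so there is no figure of its own to reproduce. The check asks how much information a proportion keeps relative to a mean.

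**Inputs from the article**
- Arm sizes: "929 individuals for the intervention group and 709 individuals for the control group" (Abstract). Total 929 + 709 = 1,638, or 1,638/14 = 117 per ward on average.
- Intracluster correlation (ICC) 0.01: stated in Table 2 for systolic pressure and borrowed here for BMI.

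**Assumed inputs:** BMI normal with mean 24 and SD 4 kg/m²; cut-off at the median (24), 25 or 30; correlation r between baseline and 12-month BMI of 0.8, 0.9 or 0.95; two-sided 5% level.

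**Step 1: no baseline adjustment.** For a small shift, the share of information kept is φ(z)² / [p(1 − p)], where p is the share above the cut, z the matching normal quantile and φ the normal density.

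| Share above cut | 50% | 40% | 25% | 20% | 10% | 5% |
|---|---|---|---|---|---|---|
| Information kept | 0.64 | 0.62 | 0.54 | 0.49 | 0.34 | 0.22 |

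More than half is lost only when fewer than about 21%, or more than about 79%, lie above the cut.

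**Step 2: both analyses baseline-adjusted.** Adjustment multiplies the variance of the mean by 1 − r² and that of the proportion by 1 − b². Here b is the correlation between the two binary indicators implied by a bivariate normal. The share kept becomes the Step 1 value × (1 − r²)/(1 − b²). At a cut of 25, p = 0.401 and the Step 1 value is 0.622:
- r = 0.8, b = 0.587: 0.622 × 0.360/0.655 = 0.34
- r = 0.9, b = 0.711: 0.622 × 0.190/0.495 = 0.24
- r = 0.95, b = 0.796: 0.622 × 0.0975/0.366 = 0.17

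At the median the results are 0.35, 0.25 and 0.17. At a cut of 30 (p = 0.067, Step 1 value 0.269) they are 0.13, 0.09 and 0.06. If the proportion is adjusted for continuous baseline BMI instead of the baseline indicator, a median cut keeps about 0.41, 0.30 and 0.22.

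**Step 3: illustrative power for an assumed fall of 0.5 kg/m².** The design effect is 1 + 116 × 0.01 = 2.16, so the effective size is 819/2.16 = 379 per arm (equal arms for simplicity). The standard error of the adjusted mean is 4 × √(1 − r²) × √(2/379). The share above 25 falls from 40.1% to 35.4%.

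| r | Power, proportion above 25 | Power, mean BMI |
|---|---|---|
| 0.8 | 0.38 | 0.82 |
| 0.9 | 0.48 | 0.98 |
| 0.95 | 0.61 | over 0.99 |

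Using 929 and 709 in place of 819 per arm changes no entry by more than about 0.01.

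**Step 4: sensitivity.**
- ICC 0.03, r = 0.8: mean 0.51, proportion 0.21.
- Fall of 0.3, ICC 0.01, r = 0.8: the mean has only 0.41.
- Fall of 1.0, ICC 0.01: the proportion already reaches 0.91 to 0.99 across the three correlations.
- A t reference on 12 degrees of freedom (14 wards) lowers the 0.82 to about 0.75.

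The mean does better in every scenario, but the size of the gap depends on the inputs.

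**The case against.** The strongest reply is that the wording is one loose list in a condensed article. Cut-offs, models and scales for secondary outcomes are commonly left to the full protocol or analysis plan, and naming a proportion does not say that mean BMI will never be reported. Prevalence of risk factors is also a legitimate outcome for a policy-oriented trial whose survey is adapted from the WHO STEPwise tool. Much of this stands. The missing cut-off is not an error, and the proportion deserves its place. What remains is that the article does name the outcome metric, and for BMI it names only the less sensitive one.

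A reader might go further and infer that most of the information is discarded whatever the cut-off. The documents do not support that. Baseline adjustment is stated only for the primary analyses, and without it about 62% survives at a cut of 25 under the assumed distribution. A loss above one half needs either an extreme cut or adjustment with a high correlation.

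A reader might also extend the point to salt intake. No amount or unit is documented for salt. If it is a categorical survey item, a proportion is natural and there may be little to lose.

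**Conclusion.** The point holds for BMI, as a modest and easily remedied loss of sensitivity on one secondary outcome. The proportion keeps about 62-64% of the information at a cut near the median without baseline adjustment. With adjustment and an assumed correlation of 0.8 to 0.95, it keeps about 17-35%. Extreme cuts do worse in both cases. The direction does not depend on the inputs tried, but the size does: cut-off, SD, correlation, BMI-specific ICC and true effect are all assumed, so the power figures are illustrations.

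It does not follow that the trial would wrongly conclude that BMI is unchanged. A non-significant secondary proportion is not such a conclusion, and mean BMI can still be computed from the height and weight data. Nor would the change guarantee detection, as the weaker scenarios show. The primary systolic outcome, its sample size and its analysis are untouched.

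**What to change.** In Primary and secondary outcomes, state the BMI outcome as the between-arm difference in mean BMI at 12 months, adjusted for baseline BMI in the same random-effects model as systolic pressure. Report the proportion above a stated cut-off alongside it; there is no need to reduce the proportion to a descriptive figure. Apply the same treatment to salt intake only if the survey records an amount, and leave smoking and alcohol as proportions.

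The cost is a change of wording and one further run of a model already planned. No new data are needed, because the proportion itself requires height and weight at baseline and follow-up. As follow-up was still under way when the article was written, the change should be dated and made before outcome data are compared by arm.

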### Sample size calculation 

The sample size for the population prevalence study is estimated according to the method suggested in the WHO STEPwise approach [23]. We calculated the sample size for 95 % CI (*z* = 1.96) on the basis of a 5 % margin of error (α), a 25 % estimated prevalence of hypertension based on the latest nationwide study in Nepal [25], a design effect of 1, and a response rate of 80 %. We will include only an age group ≥ 25 years old, resulting in a total of four age groups for each sex (total strata = 8). This will result in a sample size equal to 2882. The participants in the baseline survey will be eligible to participate in the intervention study. For the intervention study, we took the reference of the mean difference and SD from studies conducted in Vietnam and Taiwan [26, 27]. As our project is randomized and includes visits by community health workers who measure blood pressure for screening additionally, we are hopeful that we will observe a 5-mmHg difference in mean SBP between the control and intervention arms. The detailed assumptions of the sample size calculation are presented in Table 2.

**Table 2 Tab2:** Sample size calculation

Category	Mean difference (mmHg)	SD	Intracluster correlation coefficient	Design effect	Clusters per arm	Individuals per arm	Total sample size
Normotensive	5	18.8	0.01	1.57	7	406	812
Prehypertensive	5	13.6	0.01	1.23	7	168	336
Hypertensive	5	15.7	0.01	1.34	7	245	490

### Intervention

After randomization, the FCHVs participating in the intervention wards will receive a 5-day training package featuring (1) introduction and importance of noncommunicable disease and/or hypertension; (2) identifying populations at risk using a checklist comprising level of salt intake, physical inactivity, smoking, and alcohol consumption; (3) blood pressure screening by using digital sphygmomanometers, height and weight measurement, and referral for those whose blood pressure is > 140/90 mmHg; (4) providing health education in major risk factors; and (5) recording, reporting, and follow-up. Educational sessions are guided by use of the Health Belief Model [28], and training materials will be developed by involving local major stakeholders. The developed materials will be pretested with the FCHVs of Pokhara Municipality.

After receiving the training, the FCHVs will be given a digital sphygmomanometer, manual weighing scale, clinical measuring tape for height, an FCHV manual, and a recording register. During the training program, FCHVs will allocate the households themselves. On average, 1 FCHV will visit 25 households (13 normotensive, 5 prehypertensive, and 7 hypertensive). Each FCHV will visit selected households three times during 1 year, where the FCHV will provide counseling and measure the blood pressure as well as the height and weight of selected respondents. If the participant is hypertensive, the FCHV will ask the respondent to visit the health facility for further diagnosis and treatment. For hypertensive participants, the FCHV will also monitor whether the respondent is taking medicine as per the advice of health care workers. Participants in the control clusters will receive usual care. Usual care means current practices related to hypertension management at the community level. After the 1-year period of the intervention, a follow-up survey will be carried out through trained professional health workers such as nurses and health assistants.

### Minimization of contamination

The risk and level of contamination will be monitored at the levels of FCHVs and participants. FCHVs will be instructed not to share information about the study and not to provide any support to people from other clusters in the community, other than the ones who are assigned. The risk of contamination will also be minimized by the cluster design, whereby the intervention and control clusters will be geographically separated and the chance of intervention cluster participants regularly meeting control cluster participants will be negligible. Further, we will collect all possible means of contamination between intervention and control participants during the follow-up survey, and, if these are found to be significant, we will make adjustments while estimating the effect.

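### The contamination rule allows an undefined, data-dependent adjustment after randomisation and is not confined to secondary analyses; on the primary SBP estimate it departs from intention to treat and can bias in either direction

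*Protocol article*

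**What the plan says.** Two sections of the protocol article bear on this.

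- **Minimization of contamination.** The investigators state that "we will collect all possible means of contamination between intervention and control participants during the follow-up survey", and then that "if these are found to be significant, we will make adjustments while estimating the effect". The section gives no contamination variable, coding, threshold or method, and does not say which estimate is to be adjusted.
- **Data analysis.** "The primary analyses will be intention to treat at the 12-month follow-up, adjusted for the baseline measure of the outcome". For chance imbalance at baseline, "we will statistically control for those differences in subsequent analyses of program effects". On the model: "The final outcome will be modeled by using random - effects regression models". Contamination is not mentioned.

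The two sections do not refer to each other. The rule for baseline imbalance is placed in later analyses; the contamination rule carries no such limit.

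**The concern.** Contamination recorded at follow-up is a post-randomisation variable. Being reached by the volunteers' counselling, blood pressure checks and referral is how the intervention is meant to work, so a model that holds exposure fixed no longer estimates the effect of assignment. People who seek out or take up such contact may also differ in SBP for other reasons, which adds confounding that randomisation does not remove.

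The decision to adjust would be taken after contamination is known, in an open trial, under an undefined criterion. Models giving very different answers could all be defended as following the protocol. At stake are the size, and under some codings the sign, of the primary SBP result.

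**Working it through.** **Design inputs from the document.** Target effect: "we are hopeful that we will observe a 5-mmHg difference in mean SBP between the control and intervention arms". Table 2, hypertensive row (difference, SD, ICC, design effect, clusters per arm, individuals per arm, total): "Hypertensive 5 15.7 0.01 1.34 7 245 490". Arm sizes: "929 individuals for the intervention group and 709 individuals for the control group will participate in the study".

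**Reproducing the plan's figures.** Design effect = 1 + (n per arm / 7 - 1) x ICC:
- normotensive: 1 + (406/7 - 1) x 0.01 = 1.57
- prehypertensive: 1 + (168/7 - 1) x 0.01 = 1.23
- hypertensive: 1 + (245/7 - 1) x 0.01 = 1.34

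All match Table 2. Totals agree: 812 + 336 + 490 = 1638 = 929 + 709. The design inputs are therefore usable. The contamination rule itself rests on no stated figure.

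**Assumptions not in the document.** The text calls contact between arms negligible and gives no rate. Assumed: 95% exposed in the intervention arm; 5% to 30% exposed in controls; exposure lowers SBP by 5 mmHg and is the only route by which arm acts; baseline correlation 0.6. Confounding is either absent or an unmeasured trait worth 4 mmHg per SD, correlated 0.5 with the propensity to be exposed.

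**Simulation.** 7 + 7 wards of 132 and 101 people (924 and 707, the stated arm sizes rounded down to equal wards), SD 15.7, ICC 0.01, random-intercept model adjusted for baseline SBP; 600 runs per setting with an effect, 1500 without. All participants are pooled at the hypertensive SD, a simplification, so the rejection rates apply to that set-up and not to each blood pressure stratum.

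Mean arm effect (mmHg) when the true exposure effect is -5:

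| Controls exposed | ITT (no confounding / confounding) | Exposure covariate, both arms: no confounding | Same: confounding | Control-only flag: no confounding | Same: confounding |
|---|---|---|---|---|---|
| 5% | -4.49 / -4.56 | +0.06 | +3.87 | -4.78 | -5.01 |
| 10% | -4.24 / -4.22 | -0.07 | +3.50 | -4.77 | -5.13 |
| 20% | -3.75 / -3.73 | +0.06 | +2.80 | -4.70 | -5.40 |
| 30% | -3.19 / -3.33 | +0.11 | +2.26 | -4.76 | -5.78 |

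**Arithmetic check.**
- ITT should equal -5 x (0.95 - c), with c the exposed proportion of controls: -4.50, -4.25, -3.75, -3.25.
- The control-only flag without confounding compares the intervention arm with unexposed controls: -5 x 0.95 = -4.75 at every c.
- With confounding, the unflagged controls have higher SBP by 4 x 0.5 x f/(1 - c), where f is the standard normal density at the cut-off. At c = 0.30, f = 0.348 and the shift is 2 x 0.348/0.70 = 0.99, giving -4.75 - 0.99 = -5.74 against -5.78 simulated.

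**Sign and power.** With the both-arm covariate and confounding, the sign was wrong in 97% to 99% of runs. Without confounding the estimate is centred near zero, and adjusting only when the covariate has p < 0.05 left a significant arm effect in 3% to 7% of runs, against 82% to 98% for ITT. With the control-only flag the sign never reversed.

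**No true effect.** ITT rejected in 2% to 4% of runs. With confounding, adjusting if p < 0.05 rejected in 57% (10% exposed) and 39% (30% exposed) under both-arm coding, in the direction of apparent harm. Under the control-only flag at 30%, the estimate was about -0.9 mmHg and rejection rose from 3% to 9%. Without confounding, neither coding biased the null.

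**The case against.** The strongest reply is that the contamination section never says the adjustment replaces or enters the primary model. It could sit beside intention to treat as a secondary analysis, and an analysis plan that is not shown may define it. That is fair. A reader might infer that the plan breaks intention to treat outright; the document supports this only conditionally, if the adjustment is applied to the primary estimate.

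Second, a reader might infer a significance test and a regression covariate. The text names neither. *Significant* may mean material, and an instrumental-variable correction would also be an adjustment. This stands.

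Third, a reader might infer that the rule erases or reverses a real effect. Erasure needs exposure coded in both arms, with most of the intervention arm counted as exposed; reversal also needs confounding. The usual meaning of contamination is controls reached by the intervention. Flagging only those moves the estimate away from zero and, without confounding, nearer to the assumed -5 than ITT is. This stands too: the direction of bias is undetermined.

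Fourth, the document expects little contact between arms and takes steps to prevent it, so the rule may never be triggered. That lowers the likelihood but does not repair the rule. Even at 5% exposed controls, the both-arm coding moved the estimate from about -4.5 to about 0.

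What the reply does not remove is that the article states a rule: it says that the effect estimate will be adjusted on a post-randomisation finding, and it sets no limit that protects the primary analysis.

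**Conclusion.** The concern holds in conditional form. The contamination rule has no defined trigger or method and is not confined to secondary analyses. Applied to the primary SBP estimate, it conflicts with the intention-to-treat analysis in the Data analysis section and makes the model depend on the data.

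The bias can go either way. Against an ITT estimate of about -4.5 to -3.2 mmHg, adjusted estimates ran from +3.9 to -5.8 mmHg according to coding and confounding, and a control-only flag could create a benefit of about 0.9 mmHg where none exists. These sizes rest on assumed exposure rates and confounding strength and show what the rule permits. They do not predict this trial's result. The document does not support the reading that intention to treat is abandoned or that the effect will necessarily be erased or reversed.

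**What to change.** In both Minimization of contamination and Data analysis, state that the primary estimate is the intention-to-treat difference in SBP adjusted for baseline SBP, with no contamination term, whatever contamination is found. Report contamination by arm descriptively. Confine any contamination-corrected estimate to one secondary or sensitivity analysis, with its variable, coding and method fixed before outcome data are analysed.

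One option is a complier-average effect with randomised arm as the instrument. In the simulation at 20% exposed controls, this is ITT divided by the difference in exposure: -3.75/(0.95 - 0.20) = -5.0, the assumed effect. It relies on arm acting only through exposure.

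The cost is a sentence in each section and one secondary analysis. The primary estimate may be diluted: on these assumptions it falls from -4.5 to about -3.2 mmHg as exposed controls rise from 5% to 30%. It kept its sign on average and was significant in about 98% down to 82% of pooled runs. The Trial status section describes the trial as ongoing, with endpoint assessment still to be completed, so at that point the rule could be settled before the outcome analysis. Asking the contamination questions only after blood pressure is recorded is an optional refinement, not part of this fix.
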